In clinical practice, patients are briefed about the treatment including potential risks in the informed consent. Although a great achievement towards patient autonomy, standard informed consent procedures may facilitate negative expectations which can, in turn, cause nocebo effects [18]. As reported in a meta-analysis, negative pre-treatment expectations predict the occurrence of actual side effects [19]. The strongest associations between symptom expectation and symptom occurrence were found for pain, fatigue, and nausea [19]. Moreover, negative treatment expectations prior to chemotherapy are high. In a study by Hofman and colleagues [20], most of the cancer patients expected that they would develop severe or long-lasting side effects such as fatigue (90.6%) and nausea (78%). In summary, optimizing informed consent procedures may be an essential module in the prevention of nocebo effects during chemotherapy.

By acknowledging the ethical and legal necessity of informed consent on the one side and the importance to minimize risks on the other, Barsky and colleagues [21] suggested educating patients about the nocebo effect. When aware of the existence of expectation-induced nocebo effects, patients’ risk of misattributing unspecific symptoms to the treatment may be lower and they may be less vigilant to bodily signals, which again, may decrease the number and intensity of symptoms [22]. First evidence has shown that informing participants about the nocebo effect led to a reduction of symptoms that were allegedly caused by wind turbines [23]. Despite the high relevance of preventing nocebo effects during routine chemotherapy treatments, no comparable research has yet been conducted in the clinical context.

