The primary aim of this exploratory clinical trial is to investigate the effects of a nocebo-education on the patient-rated number and intensity of side effects in gastrointestinal cancer patients undergoing chemotherapy. By suggesting that side effects are not thoroughly determined by the pharmacodynamics of the treatment, patients’ perceived self-efficacy to control side effects may be increased, and the misattribution of ambiguous body signals to the treatment may be reduced. Additionally, the nocebo-education may also facilitate the development of positive expectations in general, which in turn, can improve health outcomes [24]. Thus, we will investigate, as secondary outcomes, patients’ perceived coping with side effects, tendency to misattribute symptoms, compliance intention, attitude towards the chemotherapy, clinician-rated severity of toxicity and type of co-medication used to treat side effects. Furthermore, we will examine whether optimized treatment expectations mediate the hypothesized beneficial effects of the nocebo-education. Since monitoring information coping styles have been associated with a higher report of side effects [25], we will investigate treatment information seeking as a moderator.

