#### Mediating variables

Expected side effect intensity and expected coping with side effects are assessed with a modified version of the GASE [34] before (T1-pre) and after the intervention (T1-post). Patients indicate the expected intensity and coping for each of the 7 symptoms (0 ‘*not at all*’ to 10 ‘*very much*’).

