### Statistical methods

All outcome analyses will be conducted for the intention-to-treat sample. Missing values will be imputed using the expectation-maximization algorithm. We will conduct ANCOVA for the primary outcomes number and intensity of side effects, and for the secondary outcomes coping with side effects, tendency to misattribute symptoms, compliance intention, attitude towards chemotherapy, and medical toxicity at both time points (10 days and 12 weeks) with adjustments for the stratum distress and for cancer staging. Logistic regression will be conducted for the secondary outcome co-medication to treat side effects with the same set of covariates. The T1-pre to T1-post changes in expected side effects and expected coping with side effects will be examined as mediators of the effect of group on the outcomes. Exploratory analyses will be conducted to compare the expected efficacy of the chemotherapy between groups using independent t-tests.

Moderate analyses will be carried out by including the group x information coping style interaction in the ANCOVA. Sensitivity analyses will be conducted under exclusion of (1) patients of the nocebo-education group who either indicated to not have heard about the nocebo effect or who gave a wrong description and (2) patients with tumor progression.

No interim analyses will be conducted.

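### The mediator is the raw T1-pre to T1-post change in expectations and no baseline-expectation covariate is named; unless T1-pre expectation is conditioned on, the indirect effect can be attenuated

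*Protocol article*

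**What the plan says.** Statistical methods fixes the mediator: "The T1-pre to T1-post changes in expected side effects and expected coping with side effects will be examined as mediators" of the group effect. The Abstract also frames the mediation question as a change in expectations across the session.

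The same section names covariates for two other analyses. The ANCOVAs are run "with adjustments for the stratum distress and for cancer staging", and a logistic regression is used for "co-medication to treat side effects with the same set of covariates". The mediation sentence that follows names none.

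Under Mediating variables and in Table 1, both expectation scales are collected at T1-pre and T1-post: "Patients indicate the expected intensity and coping for each of the 7 symptoms", each on a 0 to 10 scale. Table 1 shows side effects themselves only at T2 and T3, so no baseline value of the outcome could stand in for baseline expectation.

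The rationale concerns levels. The Background cites a meta-analysis in which "negative pre-treatment expectations predict the occurrence of actual side effects", and gives the aim as: "we will examine whether optimized treatment expectations mediate the hypothesized beneficial effects of the nocebo-education". The pilot effect in Sample size calculation is a group difference in post-session expectations, again a level.

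**The concern.** Patients who arrive expecting many side effects have the most room to fall, so they tend to show the largest drop. On the protocol's own reasoning they also tend to report more side effects. Baseline expectation is then a common cause of the mediator (change) and the outcome. Randomisation protects the path from group to mediator, but not the path from mediator to outcome.

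If the analysis is run as literally written, with at most distress and staging as covariates, the coefficient of change can be pulled towards zero. The missing part is booked as a direct effect of the session. Mediation by expectations is the trial's test of its proposed mechanism, so the risk is a report that expectations explain little of a benefit when they explain much of it.

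**Working it through.** **The plan's own figure.** For d = 0.60, two-sided alpha 0.05 and 80% power, the normal approximation gives 44 per group. The exact t-test gives 44.6, so 45 (power 0.804), and 90 / 0.90 = 100. The stated sample size reproduces. The document states no figure for the mediated effect.

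**Set-up.** Within group, let X be T1-pre expectation (SD 1) and M be T1-post expectation (SD k), with correlation ρ. Let C = M − X be the change. The outcome is Y = bM + cX + error, where b is the effect of post-session expectation and c any remaining effect of pre-session expectation. The session shifts M by a. The values of ρ, k, b and c are assumptions. For a, the pilot's design value of 0.60 is used as a proxy, in SD units.

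**Change and baseline.** Cov(C, X) = ρk − 1, which is negative whenever ρk < 1.

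**Slope on raw change, baseline omitted.** Slope = Cov(Y, C) / Var(C), so the share of b recovered is

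[k² − ρk + (c/b)(ρk − 1)] / (1 + k² − 2ρk).

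With k = 1 the slope is (b − c)/2 for any ρ. Worked values with c = 0:
- k = 0.8, ρ = 0.3: (0.64 − 0.24) / (1.64 − 0.48) = 0.40 / 1.16 = 0.34
- k = 0.8, ρ = 0.8: (0.64 − 0.64) / (1.64 − 1.28) = 0
- k = 1.2, ρ = 0.3: (1.44 − 0.36) / (2.44 − 0.72) = 1.08 / 1.72 = 0.63
- k = 1.2, ρ = 0.8: (1.44 − 0.96) / (2.44 − 1.92) = 0.48 / 0.52 = 0.92

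Share recovered as ρ goes from 0.3 to 0.8:

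| c/b | k = 0.8 | k = 1 | k = 1.2 |
|---|---|---|---|
| −1 (change itself drives Y) | 100% | 100% | 100% |
| 0 (only post level matters) | 34% to 0% | 50% | 63% to 92% |
| 0.5 | 2% to −50% | 25% | 44% to 88% |
| 1 | −31% to −100% | 0% | 26% to 85% |

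At ρ = 0.9 with c = 0 the share is −40% for k = 0.8 and 129% for k = 1.2, so overshoot is possible at very high correlation.

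**Where the lost part goes.** The group effect on C is still a. With b = 0.3, c = 0 and k = 1, the true indirect effect is −0.6 × 0.3 = −0.18. Raw change returns −0.6 × 0.15 = −0.09, and the other −0.09 appears as a direct effect.

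**With baseline included.** bM + cX = bC + (b + c)X. Once X is in the model the slope on C is b, the same as the slope on M, and nothing is lost.

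**Simulation.** 45 per arm, 3,000 runs per setting, a = −0.6, b = 0.3, k = 1, ρ = 0.5. A binary distress covariate, built from a score correlated 0.4 with baseline expectation, is in every model. Power means both paths significant at 5%.

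| c | Raw change: indirect (share) | Power | T1-pre added: indirect | Power |
|---|---|---|---|---|
| 0 | −0.099 (55%) | 0.26 | −0.183 | 0.64 |
| 0.15 | −0.057 (32%) | 0.11 | −0.182 | 0.66 |
| 0.3 | −0.015 (8%) | 0.05 | −0.182 | 0.71 |
| −0.3 | −0.177 (98%) | 0.64 | −0.178 | 0.62 |

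At ρ = 0.7 the raw shares are 54%, 32%, 7% and 101%. At c = 0 power is then 0.19 raw against 0.52 adjusted. Distress adjustment helps little: 54–55% recovered instead of 50% at c = 0.

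**The case against.** The strongest reply is that the document never says T1-pre expectation is left out. The two named covariates belong to the ANCOVA and logistic models, and the mediation sentence is one line of a condensed article. If T1-pre is in the mediation models, the change score does no harm. This stands. A reader might infer that the plan excludes baseline expectation, or that choosing a change score is in itself the error; the document supports neither. What remains is that the change score is a stated choice, made in two places, with nothing beside it to make it safe.

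Second, the authors may mean change as the mechanism. If change alone drives side effects (c = −b), the raw slope is unbiased. This stands as a possibility but fits the rationale poorly. With equal SDs it implies a within-group slope of side effects on T1-pre expectation of b(ρ − 1), which is negative: patients arriving with worse expectations would report fewer side effects. In fairness, the Background does not separate expectations before the session from those after it, so it does not establish a separate baseline effect c either.

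Third, the size rests on inputs that the document does not give. This also stands.

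Fourth, mediation is a further analysis in a self-described exploratory trial. True, and it limits the weight of the point.

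**Conclusion.** The point holds in conditional form. If T1-pre expectation is not conditioned on, the mediator-outcome path is confounded under the level mechanism that the protocol leans on. The indirect effect can then be attenuated, with the difference moving to the direct effect. Recovery is half if pre and post SDs are equal and only the post-session level matters. Over the correlations of 0.3 to 0.8, SD ratios of 0.8 to 1.2 and baseline effects tabulated, it runs from below zero to 100%.

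A reader might go further and conclude that the mediated effect will be halved or lost. The document does not support that. Exact halving needs equal SDs and c = 0. Near-total loss needs pre-session expectation to matter about as much as post-session expectation over and above it, or a smaller post-session SD with high correlation. None of these inputs is reported.

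The group-to-mediator path is unbiased under randomisation either way. The primary comparison, the secondary outcomes and the sample size of 100 are untouched.

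**What to change.** State in Statistical methods that the mediator model and the outcome model each include the T1-pre score of the same expectation scale, together with distress stratum and cancer staging. Use the T1-post score as mediator or, equivalently once T1-pre is included, the change. If the full analysis plan already does this, the sentence only makes it explicit.

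The cost is one sentence and one extra covariate per model. No new data are needed. In the simulated settings, the adjusted analysis lost little power even where raw change was unbiased (0.62 against 0.64 at ρ = 0.5; 0.51 against 0.55 at ρ = 0.7).

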### Randomization and blinding

A stratified block randomization is performed after the signing of the informed consent. To prevent a potential selection bias due to predictability, the block sizes are not noted here. The stratum distress is assessed at T1-pre using a distress-thermometer, a commonly used screening instrument among oncological patients ranging from 0 (not distressed) to 10 (extremely distressed) [27]. The allocation sequence for each stratum category (distress < 5 ‘low’ vs. distress ≥5 ‘high’) is produced by a research assistant prior enrolment using a computer program [28]. Sequentially numbered, opaque, sealed envelopes are used for the concealment of group assignment. Randomization is performed by a trained healthcare professional who, according to the distress level indicated by the patient, draws the envelope from the respective box. Patients are present during the allocation and are informed about their assignment instantaneously.

Due to the nature of the study, patients are not blinded. However, they are unaware of the specific study hypotheses and the content of the intervention that they do *not* receive. The trained healthcare professional is not blinded to group assignment. However, we aimed to confine the post-randomization interaction between the trained healthcare professional and the patient to the intervention. Follow-up assessments are conducted independently via mail using a standardized cover letter, i.e., no further interactions take place. Only in cases when patients do not complete assessment, the healthcare professional conducts a reminder call which is manualized in advance.

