#### Manipulation check, evaluation of the nocebo-education, process variables

Comprehension of the nocebo effect information is reviewed by asking patients in the nocebo group to describe the nocebo effect. Perceived relevance of the nocebo-education and the control intervention is assessed at T1-post. Expected efficacy of chemotherapy includes four items that assess to which degree the patient anticipates the treatment will 1) help them recover, 2) shrink the tumor, 3) improve their quality-of-life and 4) prolong their life. Each item ranges from 0 (*not at all*) to 10 (*very much*). Progression of cancer is assessed from medical records during the study period.

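### Expected efficacy of chemotherapy is compared by unadjusted t-tests, although randomisation is stratified by distress and the main outcome models adjust for distress and stage; precision may be lost

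*Protocol article*

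**What the plan says.** Four places in the protocol article bear on this.

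- **Statistical methods**, on this variable: as an exploratory analysis, the plan is to "compare the expected efficacy of the chemotherapy between groups using independent t-tests". No covariates are named.
- **Statistical methods**, on the other outcomes: the ANCOVAs for the primary outcomes and the continuous secondary outcomes are fitted "with adjustments for the stratum distress and for cancer staging". The binary outcome follows the same rule: "Logistic regression will be conducted for the secondary outcome co-medication to treat side effects with the same set of covariates".
- **Randomization and blinding**: "A stratified block randomization is performed after the signing of the informed consent". The only stratification factor is the distress thermometer, split at 5. Cancer stage is not a stratification factor.
- **Manipulation check, evaluation of the nocebo-education, process variables**: "Expected efficacy of chemotherapy includes four items", each scored 0 to 10, on recovery, tumour shrinkage, quality of life and survival. Table 1 ticks this measure at T1-post only, so it has no baseline value.

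**The concern.** The protocol states one adjustment rule for its outcome models and then drops it for this comparison without giving a reason. Attitude towards the chemotherapy, a related 0-to-10 self-rating, is analysed with the adjusted ANCOVA.

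Two mechanisms are involved, and they differ.

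- **Distress.** Stratified blocks keep distress nearly balanced between arms, so it adds little to the true variability of the group difference. A t-test still counts the spread between strata as noise. If distress predicts the answers, its standard error is too large and the test rejects too rarely.
- **Stage.** Stage is not balanced by design, so the t-test's standard error correctly includes chance imbalance in stage. Adjusting for it would remove that variation and narrow the interval, if stage predicts the answers. That is plausible for items on recovery and survival, but the protocol gives no figures.

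At stake is the width of the intervals for four exploratory comparisons, not their validity.

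**Working it through.** **1. The plan's own figure.** Sample size calculation gives d = 0.60, two-sided alpha 0.05, power 80%, 45 per group, and 100 in total with 10% dropout. The exact noncentral t gives power 79.5% at 44 per group and 80.4% at 45, so 45 is right. 90 / (1 − 0.10) = 100. The figure reproduces. It sizes the primary outcome; none is given for expected efficacy.

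**2. Number of patients.** Expected efficacy is collected right after the session, before follow-up dropout can act. I assume about 50 per arm (100 randomised 1:1), not the 45 left after dropout.

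**3. Formula.** Let R² be the share of outcome variance explained by distress stratum and stage. The residual SD is SD × √(1 − R²), so the standard error and the detectable difference scale by about √(1 − R²). I take 1 df for distress and 3 for stage (four categories, assumed), leaving 98 − 4 = 94 residual df. At 50 per arm and 80% power, the unadjusted detectable d is 0.566.

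The protocol gives no R², so every R² below is assumed. The power column uses an illustrative effect of d = 0.50, also assumed.

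| R² | √(1 − R²) | Detectable d, 50 per arm | Power at d = 0.50 |
|---|---|---|---|
| t-test | – | 0.566 | 69.7% |
| 0.02 | 0.990 | 0.560 | 70.5% |
| 0.05 | 0.975 | 0.552 | 71.9% |
| 0.10 | 0.949 | 0.537 | 74.2% |
| 0.20 | 0.894 | 0.506 | 79.0% |
| 0.30 | 0.837 | 0.474 | 84.1% |

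**4. Simulation.** The formula ignores the small cost of chance imbalance in the covariates. A simulation includes it: 100 patients, distress split half and half, stratified blocks of 4, four equally likely stage categories (all assumed), 10,000 runs per setting. The Monte Carlo error of a 5% rejection rate is √(0.05 × 0.95 / 10,000) = 0.2 points.

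| R² distress, stage | Rejection under the null: t-test / adjusted | Power at 0.5 SD: t-test / adjusted | Standard error, adjusted ÷ t-test |
|---|---|---|---|
| 0, 0 | 4.6% / 4.8% | 68.7% / 67.6% | 1.016 |
| 0.05, 0.05 | 4.3% / 4.9% | 70.3% / 72.5% | 0.964 |
| 0.10, 0.10 | 3.8% / 5.0% | 71.1% / 77.8% | 0.909 |
| 0.20, 0.10 | 2.9% / 5.3% | 71.9% / 83.3% | 0.849 |

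The t-test never rejects too often, and it becomes more conservative as the covariates explain more. Adjustment ranges from a loss of about 1 point of power to a gain of about 11. The simulated reductions in standard error (4%, 9%, 15%) are slightly smaller than the formula's (5%, 11%, 16%).

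**The case against.** The strongest case against is that nothing here is an error. A t-test in a 1:1 randomised comparison is unbiased, and ignoring a prognostic stratum errs on the safe side. The comparison is labelled exploratory, the measure is a process variable, and a simpler test is a legitimate choice. All of this stands, and it sets the size of the point.

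Several stronger readings are tempting and are not supported.

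- **That precision is certainly lost.** This needs distress or stage to predict the answers, and the protocol reports no such association. At R² = 0 adjustment is slightly worse.
- **That the t-test is invalid, or that chance stage imbalance distorts it.** Its standard error already allows for random stage imbalance, and its type I error is not inflated.
- **That distress and stage are the only covariates available, because no baseline value exists.** Table 1 lists attitude, compliance intention, expected side effects and expected coping at T1-pre, and Baseline variables lists treatment aim. The case for distress and stage is that the plan already uses them.
- **That stage adjustment deals with the mix of neoadjuvant, adjuvant and palliative patients.** That mix is treatment aim, which the protocol records separately from staging.
- **That the detectable difference should be worked out at 45 per arm.** That is the number after follow-up dropout and does not fit a T1-post measure.
- **That this analysis is meant to show whether the education lowers confidence in the treatment.** The protocol states no such purpose.

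What survives is that the plan names a method that departs from its own adjustment rule and from its stratified design, and that aligning it needs no new data.

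**Conclusion.** The point holds as a modest gain in efficiency and consistency. The planned t-tests are valid, but conservative if distress is prognostic and less precise than they could be if either covariate is. Over an assumed R² of 0 to 0.30, adjustment takes the standard error from about 1–2% larger to about 16% smaller by formula (15% in the simulation). It takes the detectable d at about 50 per arm from about 0.57 to about 0.54 (R² = 0.10) or 0.47 (R² = 0.30). These figures rest on the assumed R², on nearly complete T1-post data and on four stage categories. At an R² of 0.02 to 0.05 the analytic power gain is only about 1 to 2 points. No primary or secondary outcome is affected, and the sample size stands.

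**What to change.** In Statistical methods, replace the independent t-tests for expected efficacy by the ANCOVA already specified for the other outcomes, fitted to each of the four items with group, distress stratum and cancer staging as terms. Keep the exploratory label. Both covariates are already collected, so the change is one of wording. The statistical cost is a few degrees of freedom: in the simulation, about 1 point of power (67.6% against 68.7%) if neither covariate is prognostic.

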## Discussion

This is the first study to evaluate whether a nocebo-education can have beneficial effects considering side effects of the chemotherapy when compared to an attention control group. Up to now, no study has evaluated whether informing patients about the nocebo effect would be useful to optimize expectations and decrease side effect load in clinical practice. If efficacious, this trial would contribute to solving the ethical dilemma posed by the necessity and importance of informing the patients about the treatment on the one side and the potential negative effects of the information on the development of side effects on the other. Our objective was to create a nocebo-information session which is short, patient-oriented, and feasible in regard to implementation into clinical routine. Also, since the nocebo-education can be provided additional to the practitioner’s information, no further changes to the clinical practice are necessary.

The following limitations should be noted: As the first exploratory trial to test hypothesized effects of a nocebo-education, the sample size in this study is rather small. Also, no specific power calculation was possible since the effects of a nocebo-education on side effects are unknown. Given the link between side effect expectations and side effects, we based our power calculations on the effects of a nocebo-education on side effect expectations. Nonetheless, the use of a proxy outcome for the sample size calculation constitutes a limitation. Due to the nature of the study, blinding of patients and healthcare professional was not possible. Whereas the healthcare professional is the assessor at T1-pre and T1-post, outcome assessments at 10 days and 12 weeks after the initial chemotherapy are conducted via mail to lessen potential biases through the assessor. Since our patient population is expected to be highly burdened, we aim to keep the additional effort which may arise through questionnaire completion to a minimum. Hence, except for our primary outcomes, we use several one-item or two-item questionnaires which have not been previously validated. Lastly, our primary outcome is based on patient self-report. If this trial shows beneficial effects of the nocebo-education, further studies including physiological measures or clinician-rated measures as primary outcomes would be valuable.

Preventing side effects of chemotherapy is essential. For example, fatigue alone can occur for months during the treatment, and for 20–34% of patients, persists up to 5 years after treatment completion [36, 37], perennially affecting quality-of-life [20, 38]. Side effects of chemotherapy are also linked to increased anxiety, insecurity and a feeling of loss of control [39]. Hence, the development of innovative interventions to reduce side effects can be beneficial for the patient in the short and in the long run, as well as for public health systems.

